#### Recruitment and screening

Potential participants are identified and enrolled through a systematic referral process from urology and oncology services at hospitals throughout the Region of Murcia. Multiple approaches are adopted to promote the program and facilitate recruitment, including training Urologists specialized in prostate cancer and radiation oncologists to provide direct patient referrals; distributing program brochures in hospitals, urology and oncology centers, and community organizations; email and postal communications to individuals who had previously contacted the Never Surrender foundation expressing interest in exercise programs; local media advertising; and dissemination through social media.

Upon initial contact, potential participants receive an information package containing detailed program information, screening documentation, and contact details for their corresponding program center. The screening process includes physician approval to ensure participant safety. Each participant´s urologist, oncologist or general practitioner completes a screening form confirming the absence of contraindications to exercise. This approach to medical clearance follows best practice recommendations for exercise program implementation in clinical populations [26].

#### Randomization

Following eligibility confirmation and informed consent, all participants complete baseline assessments prior to randomization. Participants are randomly allocated to groups using a computer-generated randomization sequence with variable block sizes (4, 6, and 8) to ensure allocation concealment and prevent prediction of future allocations [27]. Randomization is stratified by age group (< 65 vs. ≥65 years) and ADT duration (< 12 vs. ≥12 months) to ensure balanced distribution of key prognostic factors that may influence treatment response. Age stratification accounts for potential differences in exercise adaptation between younger and older adults [28], while ADT duration stratification addresses the progressive nature of treatment-related side effects, as longer ADT exposure is associated with greater muscle mass loss and functional decline [29]. An independent researcher with no involvement in participant recruitment or assessment performs the randomization procedure using a secure online randomization system.

#### Blinding

Due to the nature of the exercise intervention, blinding of participants and exercise physiologists is not feasible, which is consistent with the inherent limitations of behavioral intervention trials [30]. However, outcome assessors for objective physical measures remain blinded to group allocation where possible to minimize detection bias. All patient-reported outcome measures are self-administered electronically to eliminate potential assessor influence. Data files are anonymized using coded identifiers by an independent researcher prior to processing by study personnel, and data analysis will be conducted by statisticians blinded to group allocation [31]. To minimize performance bias, participants are informed that there is equal possibility of assignment to either treatment group, and that the relative effectiveness of two different exercise interventions is under investigation, without suggesting superiority of either approach.

### Exercise protocol of intervention group

The SPORT-PCa-ADT Program is designed following international guidelines on evidence-based exercise prescription for prostate cancer (PCa) patients undergoing ADT [13, 18]. The program is specifically tailored to counteract the well-documented adverse effects of ADT, including muscle loss, increased fat mass, decreased bone mineral density, and cancer-related fatigue. Particular attention was given to balancing physiological effectiveness with practical implementation considerations.

Subjects participate in the supervised exercise program twice weekly (with a 48–72-hour interval between sessions) for 24 weeks, totaling 48 supervised sessions. The progressive resistance training program uses velocity-based training principles [32–34], a novel approach in exercise oncology that allows for precise load management and individualization based on daily performance capacity [35]. The sessions are conducted in a specialized sports center under direct supervision of exercise physiologists and sports scientists specifically trained in the SPORT Protocol, at the same time of day (± 1 h) for each participant, and under controlled environmental conditions (20 °C and 60% humidity). The study protocol of exercise training and evaluation is shown in Fig. 2.

**Fig. 2 Fig2:**
[figure not shown]
Exercise Training Sport Protocol Intervention and Evaluation Protocols in SPoRT-PCa-ADT

#### Exercise prescription

The primary resistance exercise focuses on the squat movement pattern due to its functional relevance and capacity to engage large muscle groups significantly affected by ADT [36]. The relative intensity of the exercise is calculated using velocity-based training, with each participant training at a load corresponding to 60% of 1-repetition maximum (1RM), equating to a mean propulsive velocity of 0.92 m/s [37]. A velocity loss threshold of 10% per exercise set is established—once this threshold is exceeded, the set is finished to prevent excessive fatigue and maintain training quality [32].

Each training session includes three effective sets per participant, resulting in a total of 144 effective sets per subject throughout the program (3 sets × 48 sessions). This approach ensures standardization of training volume while accommodating individual variations in strength and fatigue. Specific components of each session include:

A standardized warm-up consisting of 5 min of treadmill running at 4 km/h, 5 min of lower body joint mobilization exercises, and two preparatory sets of six squats with 6 kg loads (with 3-minute rests between sets).The main resistance training component focuses on squat exercises using a Smith machine (without a counterbalance mechanism). Participants perform the squat starting from an upright position with knees and hips fully extended, feet parallel and shoulder-width apart, and the bar resting on the upper back at the acromion level. The descent phase is performed at a controlled mean velocity (~ 0.50–0.65 m/s) until the top of the thighs are below the horizontal plane, with posterior thighs and shins in contact (~ 35–40° knee flexion). The concentric phase is executed at maximum intended velocity.Recovery periods between sets are strictly monitored, ranging from 3 min (for lighter loads) to 5 min (for heavier loads), to ensure adequate recovery of the neuromuscular system.A 10-minute cool-down period includes light aerobic activity and dynamic stretching of the major muscle groups utilized during the session.

The dynamic measurement system (T-Force, Ergotech Consulting, Spain) provides real-time auditory and visual velocity feedback during each repetition, allowing participants to maintain the target velocity and enabling precise implementation of the velocity loss threshold. This system automatically calculated relevant kinematic parameters for each repetition and stored data for analysis [38].

#### Exercise progression and modification

While the program focuses primarily on squat exercises, supplementary exercises are incorporated based on individual participant needs and progression as determined by the supervising exercise physiologist. The program follows a periodized progression model with three distinct phases.

*Adaptation Phase (Weeks 1–4)* emphasized proper technique, movement patterns, and development of a basic strength foundation. During this initial phase, participants worked at lower intensities (50–55% of 1RM, corresponding to a mean propulsive velocity of ~ 1.0 m/s) with higher repetitions and lower velocity loss thresholds (5–7%). This conservative approach allows participants to develop technical proficiency while minimizing fatigue and soreness, particularly important for deconditioned individuals beginning an exercise program during cancer treatment.*Development Phase (Weeks 5–14)* introduced a progressive increase in training load (55–65% of 1RM, ~ 0.92 –0.85 m/s) and velocity loss thresholds (7–10%) to drive physiological adaptations. This middle phase constitutes the core of the intervention, where the greatest improvements in muscular strength, physical function, and body composition are expected to occur. The gradual progression in intensity during this phase is carefully monitored to ensure that adaptations occurred without excessive fatigue or risk of injury.*Maintenance Phase (Weeks 15–24)* focused on stabilization of training load with strategic variation in exercise selection and training modalities to prevent plateaus while maintaining adaptations. This final phase is designed to consolidate gains made during the development phase and establish sustainable long-term exercise behaviors. Small variations in exercise prescription are introduced to maintain participant engagement and prevent psychological fatigue from program monotony.

Throughout all phases, individualized modifications are made based on multiple factors. Individual response to each training session is carefully monitored through performance metrics and subjective feedback. The presence and severity of treatment-related side effects are assessed at each session, allowing for day-to-day adjustments in exercise prescription. Any pre-existing musculoskeletal conditions are accommodated through exercise modifications while maintaining program integrity. The rate of progression in strength and movement velocity is tracked longitudinally to ensure appropriate progression for each participant.

To accommodate individual variations in fatigue (particularly relevant in cancer patients), a daily readiness assessment is conducted before each session. This includes a subjective fatigue rating, measurement of resting heart rate, and performance of submaximal squat repetitions to assess movement velocity. If significant deviations from baseline are observed, the training load was adjusted accordingly to prevent overtraining while ensuring sufficient stimulus for adaptation. This responsive approach to exercise prescription allows the program to accommodate the fluctuating energy levels and symptoms commonly experienced by prostate cancer patients undergoing ADT. Additionally, we have monthly telematic meetings and direct consultations with the responsible medical team to address any doubts regarding changes in clinical status.

### Exercise protocol of control group

Participants assigned to the control group received structured written instructions for a personalized home-based resistance training program. The protocol is designed to prioritize safety, progressive adaptation, and individualization based on each participant’s functional capacity and available resources at home. The program is intended to be performed two to three times per week on non-consecutive days, focusing exclusively on lower-body training through a single primary movement. Each session consists of three effective sets of 12 repetitions, which serves as the standard training volume for the main exercise.

Each session begins with a standardized warm-up targeting the lower limbs, consisting of two sets of 15 repetitions each of seated knee extensions, seated ankle dorsiflexion and plantarflexion, and bodyweight glute bridges. Following the warm-up, participants perform box squats as the sole main exercise. This movement is chosen for its safety, simplicity, and suitability for progressive overload in a home setting. Participants are instructed to perform the concentric phase of each repetition with maximal voluntary velocity, a core element of the intervention aimed at optimizing neuromuscular engagement while limiting cumulative fatigue.

To ensure a low perception of effort and avoid excessive neuromuscular strain, the program prescribes a low-to-moderate training load, with each set performed with at least twice the number of repetitions in reserve relative to those completed. This approach is designed to maintain a subjective exertion level below 12 on the Borg 6–20 scale and to minimize velocity loss within each set. Participants are encouraged to use bodyweight or accessible household items as external resistance, depending on their capabilities and context.

Weekly telephone follow-ups are conducted by trained research staff to reinforce adherence, provide feedback, and resolve any concerns. Additionally, participants are provided with a structured training log to self-monitor their sessions and support continued engagement with the program.

### Concomitant care

All participants, regardless of group allocation, are permitted and encouraged to continue all ongoing oncological treatments as prescribed by their responsible urologist or oncologist, including androgen deprivation therapy, radiotherapy, or any other systemic or supportive treatments. No modifications to participants’ oncological treatment regimens will be made because of trial participation. Participants are asked to refrain from engaging in any additional structured resistance training program outside of the trial protocol during the 24-week intervention period, in order to avoid confounding the specific effects of the allocated exercise intervention. Unstructured physical activity of low-to-moderate intensity, such as walking or activities of daily living, is permitted and will be recorded through self-report at each assessment timepoint. Any change in oncological treatment or initiation of new pharmacological agents during the trial period will be documented and considered in the sensitivity analyses.

### Assessment protocol

All participants undergo identical assessment procedures irrespective of group allocation. Baseline assessments are conducted within two weeks prior to randomization, and post-intervention assessments are scheduled within two weeks following completion of the 24-week intervention period. Midpoint assessments of patient-reported outcomes are conducted at week 12 and are administered either at the training center or during specialized urological consultations as part of routine oncological follow-up. To reduce the influence of diurnal variation, all physical performance assessments are scheduled at the same time of day for each participant (± 1 h). Participants are instructed to refrain from strenuous physical activity for 48 h prior to testing, maintain adequate hydration, and abstain from caffeine and alcohol for 24 h before each assessment (Fig. 2).

Physical assessments are conducted by qualified sports scientists with training in exercise oncology. Due to logistical constraints, assessors are not blinded to group allocation. However, patient-reported outcomes are collected using standardized, self-administered questionnaires to mitigate potential assessor bias. Venous blood samples are drawn by certified phlebotomists and analyzed by laboratory technicians blinded to group assignment. To ensure procedural consistency, comprehensive standard operating procedures (SOPs) are developed prior to study initiation, and all research personnel complete structured training. Ongoing quality control procedures are implemented throughout the study to uphold methodological rigor.

#### Physical assessments

##### Progressive loading test

A progressive loading test is conducted using the squat (SQ) exercise to evaluate strength and velocity parameters. Participants perform the SQ starting from an upright position with knees and hips fully extended, feet parallel and shoulder-width apart, and the bar resting on the upper back at the acromion level. Each participant descends continuously until the top of the thighs were below the horizontal plane, with the posterior thighs and shins in contact (~ 35–40° knee flexion), then immediately reverses the movement to return to the upright position.

Unlike the eccentric phase, which is performed at a controlled mean velocity (~ 0.50–0.65 m/s), participants are required to execute the concentric phase at maximum intended velocity. The initial load is set at 6 kg and progressively increased in 5 kg increments until the mean propulsive velocity (MPV) reached 70% of 1RM. Strong verbal encouragement is provided to motivate participants to exert maximum effort. Recovery times between sets vary from 3 min (light loads) to 5 min (heavy loads). Only the best repetition at each load, based on the fastest MPV criteria, is considered for subsequent analysis.

All velocity measurements reported in this study correspond to the mean velocity of the propulsive phase of each repetition [37]. The propulsive phase is defined as the fraction of the concentric phase during which the bar’s acceleration exceeded gravitational acceleration [39]. A Smith machine without a counterbalance mechanism is used for testing and training. A dynamic measurement system (T-Force, Ergotech, Spain) automatically calculates relevant kinematic parameters for each repetition, provides real-time auditory and visual velocity feedback, and stores data for analysis.

##### Vertical jump test

In the countermovement jump (CMJ) test, participants perform five maximum CMJs with 20-second rests between jumps. Before CMJ evaluation, participants warm up by performing two sets of 10 squats without external load, 5 submaximal CMJs, and 3 maximum CMJs. CMJ height was calculated from flight time values determined using a contact platform (Chronojump Boscosystem^®^, Barcelona, Spain). After discarding the highest and lowest CMJ heights, the resulting average is retained for further analysis. This test serves as a measure of lower body power and neuromuscular function, which are commonly impaired in patients undergoing ADT.

##### Maximum isometric contraction test

Maximum isometric force (MIF) and maximum rate of force development (RFDmax) are measured during a maximum voluntary isometric contraction (MVIC) test in the squat (SQ) exercise with participants standing and knees flexed at 90° (180° = full extension). This test is performed on a quadriceps extension machine. Participants are instructed to push against the force platform as quickly and forcefully as possible following the “ready, set, go!” signal during two 5-second trials separated by 1-minute rests. External forces are recorded at a sampling rate of 1000 Hz and processed using specific software (Chronojump Boscosystem^®^, Barcelona, Spain). RFDmax is calculated as the maximum slope in the time-force curve over 20 ms intervals. Additionally, the average tangential slope of the time-force curve is obtained at different time intervals (50, 100, and 150 ms from the onset of force production, RFD0-50, RFD0-100, and RFD0-150, respectively) was calculated. The average value of each variable from the two attempts is recorded.

#### Patient-reported outcomes

*Fatigue assessment*: Cancer-related fatigue, one of the most common and debilitating side effects of cancer treatment and ADT, is assessed using the Brief Fatigue Inventory Short form (BFI-SF). This validated 9-item questionnaire measures the severity of fatigue and its interference with daily activities. Scores are categorized as mild (1–3), moderate (4–6), or severe (7–10) fatigue. The BFI-SF sf has demonstrated excellent reliability and validity in cancer populations and is sensitive to changes following exercise interventions [40].*Quality of Life Assessment*: Quality of life is evaluated using the Functional Assessment of Cancer Therapy-Prostate (FACT-P) questionnaire. This 39-item instrument comprises the FACT-General (FACT-G) plus a prostate cancer subscale (PCS) that assesses concerns specific to prostate cancer and its treatment. The FACT-P evaluates physical wellbeing, social/family wellbeing, emotional wellbeing, functional wellbeing, and prostate cancer-specific concerns. Higher scores indicate better quality of life. This instrument has been extensively validated in prostate cancer populations and demonstrates good sensitivity to change following interventions [41].*Psychological Distress*: Psychological distress is assessed using the Hospital Anxiety and Depression Scale (HADS), a 14-item questionnaire designed to identify anxiety and depression in patients with physical health problems. The scale produces separate scores for anxiety and depression. The HADS has been validated in cancer populations and is widely used in psycho-oncology research [42].*Urinary Function*: Urinary function, which can be affected by both prostate cancer and its treatments, is assessed using the International Prostate Symptom Score (IPSS). This 8-item questionnaire evaluates the severity of lower urinary tract symptoms associated with benign prostatic hyperplasia and other conditions affecting urinary function in men. The total symptom score ranges from 0 to 35, with higher scores indicating more severe symptoms. Additionally, includes an ancillary query regarding the patient’s quality of life related to urinary symptoms, thereby providing a comprehensive evaluation that supports both diagnostic and therapeutic decision-making in clinical practice [43].*Sleep Quality*: Sleep disturbances are common in cancer patients and can significantly impact quality of life. Sleep quality is assessed using the Pittsburgh Sleep Quality Index (PSQI), a 19-item self-report questionnaire that evaluates sleep quality and disturbances over a one-month period [44]. The PSQI generates seven component scores and a global score from 0 to 21, with higher scores indicating worse sleep quality.

#### Additional clinical measures

*Anthropometrics*: Height is measured to the nearest 0.1 cm using a wall-mounted stadiometer. Weight and body composition are measured through an 8-electrode segmental monitor (TANITA, Tokyo, Japan). In addition, body mass index (BMI) is calculated as weight (kg) divided by height squared (m²). All measurements are taken in duplicate, and the average are used for analysis.*Biomarkers*: Blood samples are collected after an overnight fast at baseline and post-intervention to assess biomarkers relevant to prostate cancer and exercise response. Prostate-specific antigen (PSA), hemoglobin (Hb), lymphocyte-to-neutrophil ratio (LNR), and alkaline phosphatase levels (LDH) are analyzed. Additionally, to evaluate exercise-induced changes in oxidative stress and inflammatory markers, high-sensitivity C-reactive protein (hsCRP) and interleukin-6 (IL-6) are assessed. All samples are processed and analyzed according to standardized procedures.

### Program monitoring and safety

The incidence and severity of adverse events during exercise sessions are systematically monitored and reported by supervising exercise physiologists using standardized documentation. Events are classified by type and severity, with participants also self-reporting any adverse events between sessions. A Data Safety Monitoring Board reviews all events to ensure participant safety, with serious adverse events are reported to the institutional Ethics Committee immediately upon identification and formally documented within 24 h.

Exercise adherence (percentage of scheduled sessions attended) and protocol compliance (actual loads, repetitions, and velocity parameters) are tracked to calculate total training volume and intensity received by each participant. Program adherence of ≥ 85% is required for per-protocol analysis, with strategies to maximize adherence including follow-up calls, flexible scheduling, and transportation assistance when feasible. Participants can withdraw at any time without prejudice to their ongoing care, and investigators can withdraw participants if they meet exclusion criteria or if continued participation is deemed potentially harmful.

No formal interim efficacy analyses are planned for this trial. Given the nature of the intervention and the study population, no independent Data Safety Monitoring Board (DSMB) has been constituted. Safety monitoring will be conducted by the principal investigator and the supervising exercise physiologists throughout the 24-week intervention period. Early termination of the trial may be decided by the principal investigator in consultation with the Clinical Research Ethics Committee of the University Clinical Hospital ‘Virgen de la Arrixaca’ if: (i) there is clear evidence of harm attributable to either intervention; (ii) enrolment falls below 50% of the target sample after 12 months of active recruitment; or (iii) continued participation is deemed clinically unjustifiable. All decisions regarding early stopping and their rationale will be formally documented.

Upon completion of the 24-week intervention, all participants — including those in the control group — will receive an individualised exercise prescription developed by the supervising exercise physiologists, based on their post-intervention assessment results. This provision ensures equitable access to evidence-based exercise support regardless of group allocation and is consistent with the ethical principle of beneficence in clinical trial design. In the event of a participant suffering harm directly attributable to trial participation, standard institutional indemnity provisions of the University Clinical Hospital ‘Virgen de la Arrixaca’ will apply. No additional financial compensation beyond standard clinical care is foreseen.

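### The safety section both relies on a Data Safety Monitoring Board and says none was constituted, and it describes systematic adverse-event recording only for supervised sessions

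*Protocol article*

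**What the plan says.** Both statements about oversight stand in the section Program monitoring and safety. The first paragraph says "A Data Safety Monitoring Board reviews all events to ensure participant safety"; the same sentence goes on to send serious adverse events to the Ethics Committee at once, with a written record within 24 hours. The third paragraph says "no independent Data Safety Monitoring Board (DSMB) has been constituted", and continues: "Safety monitoring will be conducted by the principal investigator and the supervising exercise physiologists throughout the 24-week intervention period".

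On recording, the section opens: "The incidence and severity of adverse events during exercise sessions are systematically monitored and reported by supervising exercise physiologists using standardized documentation". It adds a second route, with "participants also self-reporting any adverse events between sessions".

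The arms differ in who is present at a session. Exercise protocol of intervention group sets two sessions a week for 24 weeks, "totaling 48 supervised sessions", and Exercise progression and modification has treatment side effects checked at each of them. Exercise protocol of control group has participants train at home two to three times a week with a training log. Staff contact is by telephone: "Weekly telephone follow-ups are conducted by trained research staff to reinforce adherence, provide feedback, and resolve any concerns".

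The third paragraph of the safety section also lists grounds for ending the trial early. The first is clear evidence that one or other of the two programmes has caused harm.

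**The concern.** There are two linked problems.

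The first is a contradiction about oversight. A reader of the first paragraph would believe that a board looks at every event. A reader of the third would believe that the principal investigator and the people who deliver the supervised programme do so. If the third paragraph is right, the stated safeguard is absent and no one is explicitly given the task of reviewing all events.

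The second is that the recording method follows the observers, and the observers attend one arm. If harms during home training are recorded less completely, the trial is less able to see a problem in the control arm. Any listing of events by arm could also make the supervised programme look less safe merely because it is watched more closely. The early-termination criterion on harm covers both programmes, so it needs usable data from both.

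**Working it through.** No statistical figure is at stake. The check compares the texts and counts contacts.

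**Oversight**

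| Point | First paragraph | Third paragraph |
|---|---|---|
| Does a board exist? | Yes, and it reviews all events | No independent board constituted |
| Who monitors safety? | Physiologists record, the board reviews | Principal investigator and supervising physiologists |
| Serious events | To the Ethics Committee, recorded within 24 hours | Not restated |
| Early termination | Not addressed | Principal investigator, consulting the Ethics Committee |

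Could the word *independent* reconcile the two? It would if an internal board existed. But the sentence that follows names those who monitor safety and mentions no board of any kind. The statements conflict on the first two rows. The last two rows do not depend on a board.

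**Recording by arm**

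The inputs are the stated frequencies in the two exercise-protocol sections.

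- Supervised sessions per intervention participant: 2 per week × 24 weeks = 48, which matches the article's own figure. All are attended by the staff who complete the standard documentation.
- Home sessions per control participant: 2 × 24 = 48 to 3 × 24 = 72. None is attended by staff.
- Telephone calls per control participant: 1 per week × 24 weeks = 24. The stated purposes are adherence, feedback and concerns.
- Self-report between sessions: stated without restriction by arm, so it applies to both. No schedule, form or prompt is given.

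The text speaks of exercise sessions in general. The limit to supervised sessions follows from who does the recording, since the supervising physiologists are not present at home sessions. The intervention arm therefore has a described systematic method plus self-report. The control arm has self-report, plus a call that may bring events to light but is not described as asking about them.

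**The case against.** The strongest reply has four parts.

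*The consequence is limited.* Serious events go to the Ethics Committee, named people monitor safety, and early termination has a decision route. None of these passes through a board. This stands. A reader might infer that all events are sent to a body that does not exist, but the article does not support that. What is unclear is who reviews the full set of events, non-serious ones included.

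*The recording point rests partly on silence.* Control participants have a weekly call that can deal with concerns, a structured log, and the same assessments as the other arm. Prompts for adverse events may sit in forms or in a full protocol that is not shown. This stands in part: recording at home is unstructured as described, not absent. But the article does specify a systematic method, and its stated observers attend only one arm. That is more than a missing detail.

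*The imbalance cannot be measured.* A reader might set 48 observed sessions against none and treat that as the difference in capture, or turn an assumed reporting rate into an apparent risk ratio. Neither is supported. The documents give no reporting rate, supervised participants also self-report between sessions, and the calls and log may capture some events. The counts describe opportunity for observation only.

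*No comparison of harms is planned.* Statistical analyses names no between-arm test of adverse events, and the termination criterion is a judgement of cause, not a comparison of rates. This stands, so a biased safety test should not be claimed. But a judgement about harm at home still needs the harm to be recorded.

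The risk should not be overdrawn either. Table 1 excludes uncontrolled or symptomatic bone disease and requires physician clearance, the home programme is set at low perceived effort, and jumps are described as a test, not as home training.

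**Conclusion.** The contradiction about the board is certain and needs no assumption. The two statements are current text in one section and must be reconciled, because they describe a participant safeguard.

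The unequal recording is also real as described. Its direction is plausible: events at home are more likely to be missed than events in a supervised session. Its size is unknown. The point assumes that the control calls and log carry no fixed adverse-event questions; if the full protocol includes them, this part reduces to saying so in the article. It bears on the termination criterion about harm and on any safety summary by arm, not on the efficacy analysis.

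**What to change.** 1. Reconcile the two statements. If the third paragraph describes the real arrangement, change only the board clause in the first. Do not delete the whole sentence, because its second half holds the serious-event route to the Ethics Committee. If a board does exist, the third paragraph needs the correction.
2. State who reviews all events and on what schedule. A reviewer who does not deliver either programme would be preferable, but that is a recommendation and not something the contradiction requires.
3. Ask the same short fixed set of adverse-event questions once a week in both arms: in the existing call for control participants, and at one of the two existing weekly sessions for supervised participants.
4. Use these answers for any safety summary by arm and as the common evidence for the termination criterion on harm. Report events noted during supervised sessions separately.

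The cost is a text correction and a few minutes at contacts that already take place: at most 24 question sets per participant, or 52 × 24 = 1,248 over the trial at the target recruitment. No new visits are needed, and no exercise or clinical rule changes.
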